### Meeting Protocol

IDMC meetings and calls for the Appy-CDS will be organized into open, closed, and executive sessions. Definitions for each meeting type are included below. The meeting type will be identified by the project manager when it provides the IDMC Chair with the meeting agenda.

#### Open sessions

Information will be presented to the IDMC by the study investigators, with time for discussion.

#### Closed sessions

The IDMC, study statistician, and Study Project Manager will discuss confidential data from the study, including information on efficacy and safety by treatment arm.

The IDMC may decide whether to remain masked to the treatment assignments at each meeting. If the closed session occurs on a conference call, steps will be taken to ensure that only the appropriate participants are on the call and to invite others to re-join the call only at the conclusion of the closed session.

#### Executive sessions

Only the IDMC members are present to discuss study issues independently. Voting on recommendations will follow Roberts' Rules of Order (Robert's Rules of Order Newly Revised (10th Edition) by Henry M. Robert III, William J. Evans (Editor), Daniel H. Honemann (Editor), Thomas J. Balch (Editor), Sarah Corbin Robert, Henry M. Robert III, General Henry M. Robert).

If the executive session occurs on a conference call, steps will be taken to ensure that only the appropriate participants are on the call and to invite others to re-join the call only at the conclusion of the executive session.

At the conclusion of the closed and executive sessions, all participants will re-convene so that the IDMC Chair can provide a summary of the IDMC's recommendations. This process provides an opportunity for study investigators to ask questions to clarify the recommendations. The meeting is then adjourned.

### Reporting Requirements for the AppyCDS IDMC

Proper records will be collected at each IDMC meeting to ensure that there is a physical record of any and all decisions and recommendations. The required documentation for IDMC meetings for the AppyCDS includes the following:

### Initial summary

The Study Project Manager is responsible for assuring the accuracy and transmission of a brief summary of the IDMC's discussion and recommendations for the NICHD Project Officer within 48 hours of the meeting or call. The Project Officer will review this summary and approve/disapprove the recommendation(s) or request additional information. The recommendations will then be sent to the Study Project Manager and the clinical investigators.

### Formal minutes

The Study Project Manager is responsible for the accuracy the formal IDMC minutes within 30 days of the meeting or call. These minutes are prepared to summarize the key points of the discussion and debate, requests for additional information, response of the investigators to previous recommendations, and the recommendations from the current meeting.

### Action plan

If the IDMC's recommendations require significant changes or follow-up, the Study Project Manager and Study Investigators will collaborate to prepare an action plan outlining the steps required to implement the recommendations.

### Reports of IDMC Proceedings for IRBs

As Appy-CDS is a multi-center study, this committee may be required to submit reports to IRBs at each of the participating sites. The participating sites for this study are outlined in Table 9 below.

## 10) Project Organization and Management

The organizational chart and project timeline are provided in the budget justification section of this grant. As co-PIs, Drs. [name] will co-lead bi-monthly meetings of the research team at HealthPartners to ensure that all necessary tasks are completed in a timely fashion and strictly according to study protocol. Study teams from KPNC will be invited to join these project meetings via Web conference. Drs. [name] will meet with KPNC investigators in-person at least once per year. Because this project includes a staggered, 2-stage intervention (*Triage CDS* and full Appy- CDS), the development, implementation and reporting and analysis phases overlap. In **Development or Phase 1 (Months 0 to 32)**, the team will develop, pilot, and revise the Appy-CDS (triage and full) interventions, including both the EHR-based algorithms to identify and extract necessary data in real time, and the Web service algorithms that process this information and return it to the EHR, where it is retained and displayed. In **Phase 2 (Months 12 to 50)**, the *Triage CDS* will be implemented across the 2 health systems and run for 12 months. Subsequently, following randomization, the full Appy-CDS will be implemented at intervention sites and continue for 24 months. **Phase 3 (Months 27 to 60)** includes import of automated data, completion of chart reviews, data analysis, and reporting of key study results. This process will begin during the course of the 2-year full intervention and allows an additional 6 months following completion of the intervention for availability of claims data for cost outcomes. Throughout the study, there will be ongoing analysis of data as they become available, and preliminary reports on the study's conceptual models, intervention strategies, and preliminary and final results will be presented at meetings and/or reported in peer-reviewed articles.

### Strengths and Limitations of the Study

A few limitations to this study should be noted. First, unlike our ongoing work in hypertension and diabetes, the recommendations embedded in Appy-CDS are evidence- based but are not backed by national guidelines. This lack of guidelines should not be perceived as a lack of consensus on best practices for this population. In fact, surgeons and ED providers increasingly agree on the value of risk stratification and the need to limit CT for children with acute abdominal pain. Furthermore, if evidence changes or new appendicitis guidelines are released during the study, we can easily modify the Web-based clinical algorithms. Second, identifying the optimal target population for Appy-CDS using automated data from the EHR in real time is challenging. In order to make comparisons across multiple EDs, it is important to identify a similar population of patients with acute abdominal pain. In our previous multi-center studies, we overcame this obstacle by using on-site research assistants; this approach is neither feasible for the current multisite study nor scalable for widespread dissemination. In the current proposal, we will use data provided by the triage nurse along with data retrieved from the EHR to create comparable cohorts across control and intervention sites. In the development phase, we will monitor to ensure that *Triage CDS* is neither overly sensitive nor overly specific and that we are providing alerts for the “right” group of patients.

These potential limitations should be weighed against the strengths of this ambitious, timely project. Namely we are proposing to conduct a large, cluster-randomized trial in 14 general EDs, serving a diverse pediatric population across two regions. Our sophisticated Web-based EHR-linked CDS system will provide a personalized risk assessment and tailored recommendations at the point of care. This novel approach could serve as the basis for future ED interventions. Our track record supports our ability to successfully conduct the proposed project. During a 10-year period, members of our research team have developed an EHR-linked CDS that improved BP and glucose control in type 2 diabetes patients in a randomized trial, and we are currently applying this strategy to improve the recognition of abnormal blood pressure

in adolescents and to optimize management for pediatric patients with a head injury. In the field of appendicitis, we have developed and validated a rule to identify children with acute abdominal pain at low risk for appendicitis. In addition, we have successfully piloted an EHR-linked time-of-ordering alert to reduce CT use in 2 large pediatric EDs. The current proposal is a natural extension of our team's substantial previous work and expertise in CDS and appendicitis. Key elements of the intervention have been successfully used in previous projects, enabling us to immediately focus on the substantial enhancements needed to implement and evaluate the Appy-CDS.

## Dissemination

Results of this research will be presented at national meetings and in peer-reviewed journals. In addition, the investigators are available for any dissemination activities that NICHD staff deem appropriate. As risks associated with pediatric exposures to ionizing radiation are increasingly publicized, efforts to reduce these exposures will be of widespread interest. Because ED clinicians may hesitate to discharge patients with acute abdominal pain without the reassurance of a negative CT, our safety outcomes are particularly important. If successful, next steps would be broad implementation of this evidence-based, point-of-care Appy-CDS system.

### a) Purpose of Document

This document serves as a reference guide for study operations, contacts, and describes the technical details of the study intervention. This document is to be used by the Site Principal Investigators (PI), Research Assistants (RA), and/or nursing staff at each participating medical center to ensure that the study procedures are followed as uniformly as possible. It includes details regarding data collection, flow, data entry, recording and encoding of data.

### b) Yearly Medical Center IRB Reviews

It is standard policy in clinical research that all studies involving human subjects be reviewed at least annually by the Institutional Review Board(s) for all participating sites. These reviews are to be done on the anniversary of the initial reviews. Reviews may be conducted more frequently than yearly at the discretion of the various IRBs. It is the Site Investigators' with the help of site project managers or coordinators, and the Institutional Review Boards' responsibility to ensure that yearly reviews occur.

### c) Participating Sites and Contacts

Table 10 includes site contact information for each emergency department participating directly in the Appy CDS project. There are 6 sites from HealthPartners Medical Group and 11 sites from Kaiser Permanente Northern California.

## **11) Investigator and Research Staff Responsibilities**

### **a) IRB related issues**

1. Read and understand protocol and study procedures (PI/PM/RA).
2. Verify that all those required by site IRB to complete Human Subjects training and have certification on file (PI/PM/RA).
3. Submit Study for site IRB approval (PI/PM).
4. Maintain file of signature and delegated responsibilities forms (PM).
5. Maintain Essential Document Binder and Manual of Operations (MOO) (PI/PM).
6. Maintain hard copies of all patient logs (PI/PM/RA).
7. Comply with site monitoring and data oversight (PI/PM/RA).

### **b) Study related issues**

1. Educate nurses, ED physicians, fellows and residents on purpose of study and methods.
  - a. Present study at ED specific conferences, resident lectures, nursing meetings, and other staff meetings as appropriate.
2. Maintain a log of enrolled, excluded and missed-eligible patients

### **c) General Responsibilities**

1. The scientific community in general and investigators in particular, are expected to make every effort to prevent scientific misconduct.
2. Primary responsibility for ensuring the authenticity of reported data rests with the principal Investigator(s). In addition, all investigators identified as authors of a report also assume responsibility for its authenticity. An investigator must not knowingly represent as empirical observations data which are newly synthesized, or arbitrarily altered.
3. The appropriate response to a complaint of fraudulent presentation of data is to review the original experimental records. All investigators have the responsibility to maintain a record of all experimental protocols and data sufficient to allow subsequent verification. Written, detailed, and explicit procedures for data gathering, storage, retrieval and analysis must be available at all sites.
4. Principal Investigators have the responsibility to ensure proper supervision of the research not performed directly by them. Trainees must be supervised by an experienced physician, and they should be encouraged to present their studies at review sessions or seminars. Publications must give credit to all investigators involved in the research and all publications must be approved by all coauthors.

5. All sites must ensure that sufficient management controls are in effect to preclude the occurrences of all unethical scientific practices in research. Examples of violations of ethical standards include:

- a. Deliberate fabrication or falsification in the conduct or reporting of research data;
- b. Plagiarism in scientific publications or in applications for research support;
- c. Practices that seriously deviate from those commonly accepted within the scientific community for proposing, reporting or conducting research;
- d. Misappropriation of research funds.
- e. Violation of laws established for the protection of human and animal subjects.

## Appendix A: Intervention Design and Workflow at HP

The Epic triage alert is a best practice advisory (BPA) built in the HP EHR that uses automated data to identify potentially eligible study participants. Data variables include age, chief complaint, pregnancy status, and trauma status. If the patient meets the initial study criteria: chief complaint of abdominal pain, age 5-20, are not pregnant and have no history of trauma, the BPA will display in the ED triage navigator. The advisory prompts the user to click a link which will bring them to a flowsheet section form where they are to complete up to 3 questions that further filter eligibility.

### a) Capturing eligibility: Epic Triage BPA

The below figures illustrate the technical architecture of the Triage (Phase 1) Appy-CDS system at HealthPartners.

#### Triage architecture.

[figure not shown]

## b) Workflow

For patients that meet the criteria described above, a Best Practice Advisory will display.

### Event log flowsheet questions for inclusion/eligibility.

Abdominal Pain Screening  
Pediatric Abdominal

Abdominal Pain Screening - Pediatric Abdominal Pain Study

Time taken: 1429 10/13/2016 Show: All Choices

Values By

▼ Pediatric Abdominal Pain Study

Is the patient's abdominal pain diffuse (ie. "generalized")? Yes No

Does the patient have any right sided abdominal pain? Yes No Don't Know

Approximately how long has the patient had abdominal pain? 5 days or less More than 5 days

Restore Close F9 Cancel Previous F7 Next F8

Once the flowsheet rows are completed, responses will be stored in Epic. This information will be retrieved at a later point for use in the full CDS for calculating appendicitis risk.

Additionally, if nurses do not respond to the Appy triage questions, a similar alert will fire at provider login. The Appy alert will display in the general BPA section of the EHR until the questions are addressed, or an acknowledgement reason is selected, as shown below.

## Provider selects or enters reason for not completing triage questions.

Research (1 Advisory)

Based on chief complaint, patient is eligible for the Pediatric Abdominal Pain study. After you examine the patient, click the blue hyperlink below to complete up to 3 questions. If appendicitis is not part of your differential diagnosis, please select an acknowledgment reason.

Acknowledge reason:

Epigastric or left sided pain | Chronic abdominal pain | Previous appendectomy | Other reasons (add comments)

Go to Abdominal Pain Additional Assessment Questions.

Refresh Last refreshed on 9/29/2016 at 12:02 PM Accept

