Complete data for the validation of pARC were available for 1426 patients. Across seven clinically actionable risk categories (< 5%, 5-14%, 15-24%, 25-49%, 50-74%, 75-84% and ≥ 85%) the pARC score provided valid risk prediction. The AUC for pARC was 0.85 (95% CI 0.83-0.87).

**Hypothesis 1:** Among pediatric patients with abdominal pain, a triage-based trigger will identify those at risk for appendicitis with a negative predictive value ≥99% and positive predictive value ≥20%.

The purpose of the *Triage CDS* (triage-based trigger) is to reliably identify a study cohort at elevated risk of appendicitis at both the intervention and control EDs. This cohort will comprise the analytic sample used to determine the impact of the Appy-CDS system on our key outcomes of CT and ultrasound use (Hy 2 & 3) and health care costs (Hy 4). In addition, data from *Triage CDS* will be included in the appendicitis risk algorithm (as detailed above). Final content of *Triage CDS* will be based on our previous decision rule, expert opinion, and review of ED workflow; Appendix A demonstrates the questions that are included.

Assessment of the *Triage CDS* will consist of 2 steps. First, the frequency that triage nurses or providers answer questions when prompted in the EHR (pain duration <96 hours, pain on right side, history of emesis, pain with walking) will be identified. Second, among pediatric patients with complete data in the EHR, the negative and positive predictive value of the triage tool will be determined. We hypothesize that among pediatric patients with complete data, the triage tool will yield a positive

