### Identification of a cohort of patients with acute abdominal pain at risk for appendicitis (Hypothesis 1):

Using existing EHR data and simple prompts implemented at triage at all 17 sites over the 6-month pre-intervention period and 24-month trial we will identify our study cohort of children and adolescents at elevated risk for appendicitis. The algorithm underlying this tool will exclude patients with chronic abdominal pain, abdominal trauma, and/or pregnancy, because their management is beyond the scope of the proposed intervention. For patients undergoing an appendectomy within 7 days of their index ED visit, a trained, blinded nurse abstractor will review their pathology report. For patients undergoing appendectomy, appendicitis is defined by specific terminology on the pathology report, as in our previous multicenter study (consistent with appendicitis, neutrophil invasion of tissue, serosal inflammation, acute peri-appendicitis, or acute appendicitis). For patients with perforation undergoing drainage and/or intravenous antibiotics and interval appendectomy, diagnosis will be based on clinical notes from the treating surgeon. For patients transferred from the ED where they initially sought care to a facility with pediatric surgical expertise, we will seek final diagnoses and pathology reports from the receiving institution. If we are unable to verify final diagnosis, the patient will be excluded from primary analyses. These patients may be included sensitivity analyses with the diagnosis of appendicitis or not appendicitis assigned based on provider impression and imaging available at the time of ED discharge / transfer. For HPMG, outside of the study EDs, Children's Hospital would be the primary outside institution to receive transfers for further evaluation and appendectomy. Thus, we will establish a registry of patients with a discharge diagnosis of appendicitis from Children's Hospital and use a probabilistic method to determine whether these patients are matches with patients receiving care in the HPMG study EDs. KPNC uses a hub and spoke system for pediatric surgery. Among the 11 CREST sites are four pediatric surgical hubs.

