## Appendix B: Intervention Design and Workflow- KP

### a) Capturing eligibility: RISTRA

The analogous triage alert at KPNC will be implemented using the RISTRA interface existing at KPNC. For patients with a chief complaint of abdominal pain, ED providers will be trained to click on the RISTRA icon embedded within the EHR.

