| APPYCDS_triage_TM      | num(8) | sas time                                                                                                                      | Time the CDS triage displayed (if displayed)                                                                                                                                     |

|                        |        |                                                                                                                                       |                                                                                                                                                          |
|------------------------|--------|---------------------------------------------------------------------------------------------------------------------------------------|----------------------------------------------------------------------------------------------------------------------------------------------------------|
| Right_Side_Pain_triage | num(8) | 1= Any right sided abdominal pain reported from triage,
0=No right sided abdominal pain reported from triage                | Designates if any right sided abdominal pain reported by RN or MD in response to triage alert                                                     |
| Pain_diffuse           | num(8) | 1=Yes, there is diffuse or generalized abdominal pain,
0=No, the pain is not diffuse or generalized                                | Designates if the pain is diffuse or generalized                                                                                                         |
| Pain_5days_or_less     | num(8) | 1=Pain duration 5 days or less, reported from triage
0=Pain duration more than 5 days, reported from triage                        | Designates if pain duration is 5 days or less at time of ED visit                                                                                        |
| Eligible_Triage        | num(8) | 1=Eligible,
0=Not eligible                                                                                                         | Designates if patient is eligible from triage at time of ED visit. Derived variable from Right_Side_Pain, Pain_diffuse and PAIN_5days_or_less variables. |

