| Eligible_Meds          | num(8) | 1=Eligible based on medication criteria,
0=Not eligible based on medication criteria                                               | Designates if patient is eligible based on medication criteria                                                                                           |
| Eligible_Chronic       | num(8) | 1=Eligible based on chronic condition criteria,
0=Not eligible based on chronic condition criteria                                 | Designates if patient is eligible based on chronic condition criteria                                                                                    |
| MD_acknowledge_BPA     | num(8) | 43=No right-sided or diffuse abdominal pain
5=Chronic abdominal pain
8=Previous appendectomy
18=Other reasons (add comments) | MD acknowledge that patient not eligible                                                                                                                 |

|                 |        |                                                                                                                                                                                                                                                                                                                                                                                                                                                                                                                                                                                                                                                            |                                                        |
|-----------------|--------|------------------------------------------------------------------------------------------------------------------------------------------------------------------------------------------------------------------------------------------------------------------------------------------------------------------------------------------------------------------------------------------------------------------------------------------------------------------------------------------------------------------------------------------------------------------------------------------------------------------------------------------------------------|--------------------------------------------------------|

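### Hypothesis 1 is worded as the accuracy of a triage trigger, but the planned NPV and PPV pool nurse answers at triage with provider answers and drop visits in which the provider opted out

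*Combined protocol and SAP*

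**What the plan says.** Specific Aim 1 and Hypothesis 1 (Sections 2(a) and 6(a)) concern a trigger operating at triage, with goals of NPV at least 99% and PPV at least 20%. Section 6(b) describes the cohort as identified "Using existing EHR data and simple prompts implemented at triage at all 17 sites". For the analysis, Section 6(a) states that "among pediatric patients with complete data in the EHR, the negative and positive predictive value of the triage tool will be determined", and it speaks of nurses or providers answering, without separating them.

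The appendices show how the answers are obtained:

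- **HP, Appendix A(b).** The nurse is asked first. However, "if nurses do not respond to the Appy triage questions, a similar alert will fire at provider login", and it stays displayed until the questions are addressed or an acknowledgement reason is chosen. Its text reads "After you examine the patient, click the blue hyperlink below to complete up to 3 questions. If appendicitis is not part of your differential diagnosis", followed by a request to select a reason. The choices are epigastric or left-sided pain, chronic pain, previous appendectomy, and an open 'other' category with comments.
- **KPNC, Appendix B(a).** "ED providers will be trained to click on the RISTRA icon embedded within the EHR"; no nurse step is described.
- **Appendix E, Hypothesis 1 variables.** Right-sided pain is a single field, "reported by RN or MD in response to triage alert". The time stored is when the alert displayed. Provider ID and type are listed, but not who answered the screen. The acknowledgement variable is described as "MD acknowledge that patient not eligible".
- **Section 7(b), enrollment table notes.** Providers who do not complete the HP questions, and KPNC visits where RISTRA was not accessed, count as screening not completed.

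**The concern.** A predictive value belongs to a test given by a particular person at a particular moment. Here the HP nurse's answer before the provider's assessment is a triage result. The HP fallback answer, given after the examination, and every KPNC answer are not. The plan has no variable that separates the first from the second within HP.

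The complete-data rule adds a selection problem. An HP provider who does not suspect appendicitis is invited to acknowledge the alert instead of answering, and a KPNC provider may simply not open RISTRA. Where that choice reflects low suspicion, the missing visits carry less appendicitis than the ones kept. Any of them that a triage rule would have flagged are removed from the PPV denominator, and the observed PPV rises.

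At stake is what Aim 1 may conclude. Hypothesis 1 could be declared met, and the review and refinement of the trigger that Section 6(a) foresees before full implementation could be skipped, for a nurse-answered rule that misses its PPV goal. Section 6(a) also allows site-specific NPV and PPV to enter the models for Hypotheses 2 to 4 as covariates if sites differ. A difference in who answered could then pass for a difference in trigger performance.

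**Working it through.** **1. The plan's own figures (Sample size and power).** 24,603 patients, 2,634 with appendicitis, about half flagged.

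- Prevalence: 2,634 / 24,603 = 10.7% (stated as 11%).
- Flagged: 0.5 × 24,603 = 12,301.5, and the same number not flagged.
- At NPV 99%: missed cases = 0.01 × 12,301.5 = 123; PPV = (2,634 − 123) / 12,301.5 = **20.4%**.
- At PPV exactly 20%: true positives = 2,460.3; missed = 173.7; NPV = 1 − 173.7 / 12,301.5 = 98.6%.
- Ceiling on PPV with no missed case: 2,634 / 12,301.5 = 21.4%.

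The two goals are compatible, but with NPV at its goal the margin on PPV is only 0.4 points.

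**2. Effect of dropping opt-outs on PPV.** Let p be the true triage PPV, o the share of would-be trigger-positive children removed by provider opt-out, and q the appendicitis rate among them. Then

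observed PPV = (p − o·q) / (1 − o).

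The documents give none of these. Assumptions for an HP illustration: p = 18%; 30% to 50% of would-be positives reach the provider alert; providers opt out of 30% to 50% of those, so o runs from 0.3 × 0.3 = 0.09 to 0.5 × 0.5 = 0.25; q = 2% to 3%.

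| o | q | Observed PPV |
|---|---|---|
| 0.09 | 3% | (0.18 − 0.0027) / 0.91 = 19.5% |
| 0.09 | 2% | (0.18 − 0.0018) / 0.91 = 19.6% |
| 0.25 | 3% | (0.18 − 0.0075) / 0.75 = 23.0% |
| 0.25 | 2% | (0.18 − 0.0050) / 0.75 = 23.3% |

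Setting the observed PPV to 20% gives o = 0.02 / (0.20 − q), that is 11.1% at q = 2% and 11.8% at q = 3%. Above that share, a true 18% would appear to meet the goal. With other assumptions (p = 17%, o = 20%, q = 1% to 3%) the observed PPV is 20.5% to 21.0%.

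**3. Effect on NPV.** Removing would-be positives leaves the trigger-negative group unchanged. If opt-outs were instead counted as trigger-negative, starting from NPV 99% with half flagged,

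NPV = 1 − (0.01 + o·q) / (1 + o).

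For o = 0.09, q = 2%: 1 − 0.0118 / 1.09 = 98.9%. For o = 0.25, q = 3%: 1 − 0.0175 / 1.25 = 98.6%. NPV falls. Only if q is 1% or less would it hold or rise.

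**4. Is the fallback likely to matter?** In the example enrollment report for one HP site (Appendix C, six months), 130 visits had screening not completed, 83 were excluded by the screening answers and 101 were enrolled: 130 / 314 = 41.4% not completed. If a visit is counted there only when neither nurse nor provider answered, nurse non-response was at least that high. The report does not show who answered the completed screens, nor how many of the 130 were acknowledgements.

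**The case against.** The strongest reply is that this is a labelling matter. Provider completion is disclosed: Section 5(a) names the provider at KPNC, and Section 6(a) mentions nurses or providers. Performance is to be reported by site, which already separates KPNC from HP. The HP questions concern pain location and duration, not examination signs. Three of the four acknowledgement reasons describe children who would be excluded or trigger-negative anyway, so only the open category can clearly remove a would-be positive.

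Much of this stands, and it limits the point. Disclosure does not turn an answer given after the examination into a triage answer, however, and site-level reporting does not separate nurse from provider within HP. The alert ties opting out to the differential diagnosis, and the open category allows it.

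A reader might go further in several ways that the documents do not support:

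- **That NPV is inflated by physician judgement.** On the assumed 2% to 3% appendicitis among opt-outs, counting them as negatives lowers NPV.
- **That opt-outs are scored trigger-negative.** `Eligible_Triage` is derived only from the three screening answers, and Section 7(b) treats provider non-completion as unscreened. The wording of the acknowledgement variable is what needs reconciling.
- **That answers are given with test results known.** Nothing requires them to precede results, but nothing shows that they follow them.
- **That KPNC's share measures the HP defect.** Table 7 projects 4,456 of 5,668 patients (79%) at KPNC. That shows how much of the enrolled cohort is provider-screened by design, but the HP alert does not exist there.

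**Conclusion.** The concern holds as a mismatch between the hypothesis and the measurement, combined with missingness that can depend on clinical suspicion. The planned pooled figures describe ED screening by nurse or provider among completed screens, not a triage trigger. The likely direction for PPV is upward, provided that opted-out or unopened visits include would-be positives with less appendicitis than the rest. The direction for NPV is not clearly favourable.

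The size cannot be derived from the documents. The range of 19.5% to 23.3% for a true 18% rests wholly on assumed fallback, opt-out and residual-appendicitis rates, and it overstates the effect if most opt-outs carry one of the three reasons that match exclusion or trigger-negative status. It does not model KPNC visits in which RISTRA was not opened. What makes the point worth acting on is the narrow PPV margin in the plan's own inputs. HP visits answered by the nurse at triage remain valid triage data.

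**What to change.** 1. Add two variables to the Hypothesis 1 dictionary: respondent (nurse or provider) and time of answer. The HP flowsheet screen in Appendix A shows `Time taken` and `Values By` labels, so both may be retrievable.
2. Report NPV and PPV separately for nurse answers at triage and for provider-completed screens (HP fallback and KPNC), with answer timing. Apply the triage-based conclusion only to the former, or reword Hypothesis 1 as ED screening by nurse or provider if the pooled figure is to decide it.
3. State that `MD_acknowledge_BPA` cases are screening not completed, reconciling Appendix E with Section 7(b), and follow them for appendicitis under the quarterly missed-eligible review in Section 9.
4. Add a sensitivity analysis that counts only the 'Other reasons' opt-outs as trigger-positive. Counting every acknowledgement as positive would misclassify children with left-sided pain or a prior appendectomy.
5. Report the number of KPNC visits with RISTRA not opened and the appendicitis found among them.

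The cost is two variables, a few sentences in the analysis plan and two extra tables; the clinical workflow does not change. The drawback is that the nurse-only estimate uses fewer visits, from HP alone, and will have a wider confidence interval. How much wider cannot be stated, because the documents do not give the number of nurse-answered screens.
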